1.3 Overview of irinotecan

[figure not shown]
 Figure 4- Chemical structure of irinotecan

Irinotecan (CPT-11) is a semisynthetic analogue of camptothecin, originally isolated in China from an ornamental plant known as Camptotheca acuminata. It is a chemotherapeutic agent that specifically causes cell death at the S phase by binding to topoisomerase I (Topo I). The discovery and synthesis of this drug occurred in Japan in 1983, and only recently, the potent antitumor activity of irinotecan against numerous tumors has become clear. (54)

CPT-11 is a prodrug converted by carboxyl esterase into its active form SN-38, which has been used in cancer patients. Phase II studies showed an objective response rate in 32% of colorectal cancer patients. Subsequently, phase III studies consolidated the role of CPT-11 in first-line treatment in combination with fluorouracil and folic acid for the treatment of metastatic colorectal cancer (55).

MECHANISM OF ACTION

Irinotecan interacts with a topoisomerase I - DNA complex and has a specific S - phase cytotoxicity. (54) Topoisomerases reduce DNA torsion and control supercoiling that occurs in specific regions of DNA, enabling its transcription and replication. Irinotecan cleaves the phosphodiester binding of DNA, and forms a covalent binding of the enzyme to DNA, which allows another strand (double or single) of DNA to pass through the ends of the DNA. Topoisomerase I binds at this cleaved end of DNA and the complex formed Topo I-irinotecan - DNA, but alone is not lethal to cells. However, collisions with advanced replication forks cause DNA strand breaks, leading to an irreversible delay in replication and cell death. (56) The collision of the irinotecan complex with topoisomerase I with the replication process also results in delayed G2 phase by signaling the presence of DNA damage to the S-phase checkpoint mechanism of the cell cycle. (57) High concentrations of irinotecan, in non-S-phase cells, also destroy cells and this mechanism of cell death is transcriptionally mediated by DNA damage through apoptosis. (58)

RESISTANCE MECHANISMS TO IRINOTECAN

INTRACELLULAR LEVEL DECREASE OF IRINOTECAN BY INCREASED DRUG EFFLUX

Resistance to multiple drugs is the major obstacle encountered by cancer chemotherapy, it is characterized by increased expression of ATP-linked transmembrane transporters (ABC – ATP binding Cassete) such as P-glycoprotein and protein associated to multidrug resistance (MRP), which carry chemotherapeutic agents out of the cell. (59) P-glycoprotein and MRP are involved in the active efflux of SN-38 and irinotecan. (60, 61)

TOPOISOMERASE I LEVELS

Topoisomerase I is the cellular target of irinotecan, and it is acceptable that topoisomerase I cellular levels be proportional to cytotoxic effects. This idea derives from experiments with mammalian cell lines. (62, 63) Irinotecan-resistant cell lines gradually became resistant through continuous irinotecan treatments, and the total activity of topoisomerase I was reduced when compared to cell-sensitive cell lines. (64) Theoretically the expression of topoisomerase I found in various tumors may be indicative of irinotecan sensitivity. Increased levels of topoisomerase I are demonstrated in colon cancer. (64, 65) The levels of topoisomerase I found in colorectal tumors are high compared to the normal colonic mucosa suggesting a causal relationship with favorable therapy. (64)

TOPOISOMERASE MUTATIONS I

Topoisomerase I mutations are found in cells resistant to Irinotecan. (66, 67) These mutations are found in areas that may alter the DNA cleavage or DNA interactions with irinotecan.

NFΚB AND IRINOTECAN

Most chemotherapy acts by inducing the apoptotic pathway. The resistance in apoptosis induction is the main mechanism by which the cancer cell protects against cell death. (68) The activation of NFκB by TNF-α, radiation ionizing agents and chemotherapy, leads to inhibition of the apoptotic response induced by stimulation in fibrosarcoma cells. (69) It has recently been reported that the inhibitor of topoisomerase I CPT-11/SN-38 activates the pathway of NFκB in cells of fibrosarcoma and hepatocellular carcinoma. (70)

PI 3-KINASE AND IRINOTECAN

Initial studies in human hepatocellular carcinoma indicate that PI3- kinase blockade increases SN-38-induced apoptosis. (71) However, the molecular mechanisms data involved in PI3 kinase activation are still unknown.

Thus, the combination of metformin and irinotecan could prevent tumor leakage by activating mTOR.

2. Purpose and justification

In this study we are planning to evaluate the safety and efficacy of metformin combined with irinotecan in patients with recurrent or metastatic colon and rectal cancer who have failed all available conventional chemotherapy regimens and who are not candidates for surgical treatment with curative intent. These patients do not have valid therapeutic options approved by national regulatory agencies.

3. Objectives and Outcomes

Primary, secondary and exploratory objectives will be tested in the population of patients with stage IV or recurrent colorectal cancer who:

• Develop disease progression after systemic treatment including fluoropyrimidines, oxaliplatin, irinotecan, and patients without the k-ras gene mutation were also resistant to cetuximab or panitumumab.

3.1 Primary Objectives

To evaluate disease control rate (stable disease + partial response + complete response) at week 12 of treatment by RECIST v1.1 (72) and the safety of metformin + irinotecan combination in patients with stage IV colon or rectum cancer who failed chemotherapy regimens containing oxaliplatin, fluoropyrimidine, irinotecan and those with wild Kras who also failed to use cetuximab or panitumumab.

3.2 Secondary Objectives

To evaluate response duration, objective response, progression free survival (PFS), and overall survival (SG). The quality of life will be evaluated (EORTC QLQ-C30 questionnaire).

3.3 Outcomes

3.3.1. Primary outcome

The primary endpoint assessed will be disease control rate at week 12 of treatment by the RECIST v1.1 criterion in the population studied. (72)

Objective response is defined as the proportion of patients with complete response (CR) or partial response (PR) confirmed according to the RECIST v1.1 criteria, related to the total population of included patients.

3.3.2. Secondary outcomes

Secondary outcomes include overall response rate (ORR), duration of response, PFS, OS, quality of life, and tolerability. The disease control rate corresponds to the objective response rate plus the rate of stable disease patients.

Progression is defined as an increase of 20% or more in the sum of the largest target lesion diameters, or the appearance of new lesions, according to RECIST v1.1, or death from any cause.

The duration of the response will be measured from the time of CR or PR documentation (whichever is first recorded) to the date of disease progression documentation, with reference to the smallest measures recorded during the course of treatment.

The duration of stable disease will be measured from the moment therapy is started until the criteria for progression are met. The duration of stable disease is conceptually identical to the time to disease progression.

Toxicity will be classified using standard terminology criteria from the American National Cancer Institute for Adverse Events, Version 4. (NCI (73) AE v4). The performance index will be ranked according to the ECOG (US Cooperative Eastern Oncology Group) criteria.

4. Patient Selection Criteria

The target population includes adult patients with histologically confirmed (stage IV or recurrent) mCRC who have failed chemotherapy regimens containing oxaliplatin, irinotecan and fluoropyrimidine and cetuximab or panitumumab if wild Kras, and which have measurable or evaluable disease.

The investigator should ensure that patients meet all inclusion criteria and none of the exclusion criteria to enter the study. In addition, prior to the first dose of study medication, all laboratory biochemistry and hematology values must meet the inclusion criteria.

4.1 Inclusion criteria:

- Patients aged 18 years and over;

- Patients with colonic or rectal adenocarcinoma with recurrent or metastatic disease refractory to oxaliplatin, irinotecan, fluoropyrimidine-based treatment and, if wild Kras, should also be resistant to cetuximab or panitumuabe; We define refractoriness as radiological progression during or within six months of termination of treatment containing all these drugs;

- Not a candidate for any treatment with curative intent, including surgery and radiation therapy;

- Measurable or evaluable disease according to the RECIST 1.1 criteria; (72)

- ECOG 0-2;

- Appropriate haematological functions (hemoglobin ≥ 10 g / dL [5.6 mmol / L]; neutrophil count ≥ 1,500 / mm3 and platelet count ≥ 100,000 / mm3), adequate renal function (serum creatinine less than 1.5 times the limit). normal liver function) (bilirubin less than 1.5 times the normal limit; aspartate aminotransferase and alanine aminotransferase less than five times the normal limit when there is liver metastasis, or 2.5 times the normal limit when the liver is free of metastasis);

4.2 Exclusion Criteria:

- Patients with known hypersensitivity to and / or prior irinotecan and metformin therapy;

- Chronic treatment with immunosuppressive agent or corticosteroids at a dose greater than 10 mg / day of prednisone;

- Patients with known central nervous system (CNS) metastases;

- Patients with a previous diagnosis of another neoplasm, except for basal cell carcinoma of the skin and noninvasive cervical cancer;

- HIV-positive patients will be accepted if they do not have active AIDS-defining illness or AIDS-associated condition that compromises the safety of patients, with stable antiretroviral treatment and reconstituted immunity (CD4 lymphocyte count ≥200 / mm³, regardless of viral load). ;

- Chronic or acute active infection (except known HIV infection with no relevant immune repercussions);

- Patients with active bleeding or bleeding diathesis;

- Patients with any uncontrolled serious medical condition or other conditions that may affect their participation in the study;

- Patients who are taking another study medication or who have received study drugs for less than 4 weeks;

- Patients who are pregnant or nursing;

- Diabetic patients on metformin treatment;

- Absolute contraindication to loperamide use.

5. Study Design

This is a prospective phase II single arm clinical study designed to evaluate the effect of metformin with irinotecan for patients with progressing mCRC after previous treatment. The primary end point is the disease control rate (stable disease + partial response + complete response) at week 12 of treatment. The efficacy assessment will be by intention to treat. The metformin and irinotecan combination will be administered continuously until disease progression by the RECIST v1.1 criteria or in case of severe toxicity or withdrawal of consent.

This study will be conducted in Barretos Cancer Hospital. The tumor response will be evaluated in the sequence below, counting from the first day of medication infusion: 6th week, 12th week, 18th week, 24th week and every 12 weeks after, using consistent imaging techniques (CT) or MRI if patients are contraindicated for CT. The evaluation will be made by the researchers through RECIST v1.1. Discontinuation of metformin medication for three days prior to three days after infusion of any iodinated contrast media for radiological studies will be allowed at the discretion of the radiology team. This frequency of examinations is similar to that used in third-line mCRC clinical studies and arises from the need to follow more closely patients whose disease has more aggressive behavior and a greater chance of disease progression in the first few years.

Toxic effects will be analyzed according to NCI CTCAE version 4.0. (73)

The study period for each patient is defined as the day of patient inclusion until:

• The day when an event (disease progression as defined by RECIST, or death) is observed.

• The day when the patient discontinues treatment due to an unacceptable adverse event, withdrawal of consent or discontinuation of the study, or for any other reason than 21 days.

All those who discontinue treatment for any reason will be followed for survival assessment.

Patients who demonstrate disease progression during the study or who discontinue the study drug for any reason other than disease progression and withdrawal of consent (ie adverse event, administrative reasons, etc.) will be subjected to survival monitoring. The investigator or designated member will contact the patient monthly for survival information and additional antineoplastic therapies.

6. Therapeutic regimens, expected toxicity, dose modifications.

6.1 Administration of medicines

Patients will be asked to take their metformin tablets daily twice a day at approximately the same time each day and should be instructed to swallow the whole tablets with a full glass of water, not chew them. All patients should avoid eating grapefruit during the study as this may increase and prolong exposure to the study drugs.  The vomited, missed or missed doses should not be re-administered and patients should take the next dose on time following the schedule. Interruption of metformin medication for three days prior to infusion of any contrast medium for radiological studies will be allowed at the discretion of the radiology team.

Metformin will initially be administered at a dose of 1500mg / day orally for 7 days, beginning on the first day of chemotherapy infusion. Patients with good tolerance (absence of grade 3 or 4 adverse events) may have metformin dose escalated to 2500 mg / day on the eighth day of the first cycle. This metformin dose and escalation regimen is in line with the current design of metformin research on cancer treatment, either alone or in combination with conventional chemotherapies. (25) These doses are the commonly used and recommended for the treatment of patients with diabetes. type II, whether they have cancer or not.

Patients will receive irinotecan 350 mg / m^2^ intravenously, diluted in 500 mL 5% dextrose solution, in continuous infusion lasting 3 hours on D1 every 3 weeks, exactly as is done in the routine care of this service. ( 75) Prior to irinotecan infusion, the patient will receive the following medications:

1. Dexamethasone 8 mg intravenously 15 minutes before infusion;

2. Ondansetron 8 mg intravenously 15 minutes before infusion;

3. Atropine 0.25 mg subcutaneously.

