|  | The primary endpoint is the disease control rate (stable disease + partial response + complete response) at the twelfth week of treatment. The efficacy assessment will be by intention of treatment. The metformin and irinotecan combination will be administered continuously until disease progression by RECIST v1.1 criteria or in case of severe toxicity or withdrawal of consent.  Sample size was calculated according to the optimal design of Simon. Considering a DCR of 13,2% on week 12 with placebo in third line, we believe that it would be clinically significant to increase this DCR to 26,7% .Considering an alpha error of 10% and a beta error of 20%, we planned to enroll 41 patients. This study would be considered positive if at least 9 patients had disease control on week 12.  This is a multi-institutional study, and it will take place at the Clinical Research Unit of Barretos Cancer Hospital.  Metformin will be given at a dose of 1500mg / day orally for 7 days, initially, and escalated to 2500mg / day if tolerated after one week of use, plus irinotecan at a dose of 125 mg per square meter body surface area D1 and D8 every 21 days. All patients will be treated until disease progression or appearance of prohibitive toxic effects. Those with a complete radiological response (CR) may discontinue irinotecan use two cycles after the diagnosis of CR (only if a total of six cycles is reached) at the investigator’s discretion, as well as those without presenting progression after two consecutive response assessments.  Tumor response will be assessed by computerized tomography (CT) or magnetic resonance imaging (MRI) every two cycles in the combined metformin and irinotecan phase and every twelve weeks during the metformin phase alone.  Toxic effects will be analyzed according to the National Cancer Institute Common Toxicity Criteria for Adverse Events, version 4 (NCI CTCAE v4). |
| Population | The target population includes adult patients with histologically confirmed or recurrent metastatic RCC refractory to treatment with oxaliplatin, irinotecan, fluoropyrimidine and an anti-EGFr agent if it is wild K-ras. |

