| Dose, treatment cycle | Metformin will be given at a dose of 1500mg/day (two pills in the morning at breakfast and one at dinner) for seven days. If there is no prohibitive adverse effect at 1500mg/day, the dose will be increased to 2500mg/day (three pills in the morning at breakfast and two at dinner), and this dose will be maintained until PD or unacceptable toxicity. Metformin will not be administered within two days prior to contrast infusion examinations at the discretion of the radiologist to minimize the risks of lactic acidosis.  Irinotecan will be administered at a dose of 125 mg/m² intravenously D1 and D8 every 21 days. |
| --- | --- |
| Preparation and administration | Metformin will have 500mg presentation. Not dosed by weight or body surface area. Irinotecan will be diluted in 5% dextrose solution. Its infusion will be performed intravenously, lasting 90 minutes. The irinotecan infusion will be preceded by the infusion of dexamethasone 20mg and ondansetrone 16mg. |
| Schedule of visits and evaluations | Study evaluations will be performed at the screening period (D-21 to D-1), the day of study initiation (D1), at D8 of the first cycle and at D1 of the subsequent cycles. |
| Effectiveness Assessments | Tumor assessment (CT or thoracic MRI, abdominal and pelvic) will be performed every 6 weeks until the 12^th^ week of initiation of treatment and after 12 weeks or at any time during the study where clinical progression is suspected. Any suspicion of progression due to clinical deterioration should be accompanied by radiological confirmation.  All images will be analyzed locally at the centers and this interpretation will be used for all clinical decisions. RECIST criteria will be used for primary endpoint analysis. |

1. Introduction

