| Hematologic | Keep the same  dose level | Maintain the same dose level *. | Discontinue the dose until the toxicity is ≤ 1 or has returned to baseline, then resume treatment at the same dose level ***. | Drop the dose until the toxicity is grade ≤ 1 or has returned to baseline, then reduce the dose to level 1 and resume treatment ^##^. |

* To start another cycle, the neutrophil count must be greater than 1,500 / mm ^3^, platelet count greater than 100,000 / mm ^3^and hemoglobin greater than or equal to 9 g / dL. ** Patients with grade 3 hypoglycemia, fatigue / asthenia who require more than 2 weeks without metformin administration to return to grade ≤ 1 toxicity should have their dose reduced to level -1.

*** Grade 3 lymphopenia and leukopenia do not require the dose to be suspended or reduced. Grade 3 recurrent neutropenia or thrombocytopenia that persists for at least 7 days requires dose reductions to level -1 in the next cycle.

Grade 4 haemorrhage requires discontinuation of study drug.

Grade 4 lymphopenia without other dose limiting events (opportunistic infection) does not require dose reduction.

If treatment discontinuation is required and the patient is unable to resume treatment within ≤ 28 days, treatment should be discontinued and the patient will continue to be followed for tumor response rate assessment and survival follow-up.

IRINOTECAN

Dose reduction in the patient will be allowed depending on the type and severity of the toxicity found. The dose levels of irinotecan are 125 mg / m², 100 mg / m² and 75 mg / m². The dose-limiting toxicities of irinotecan are related to neutropenia, alopecia, nausea, severe diarrhea, hypersensitivity reactions, asthenia and myalgia. Considering that the clinical toxicity most commonly related to irinotecan intolerance is diarrhea, the patient will be instructed to start treatment with loperamide when experiencing grade 1 diarrhea in order to avoid severe diarrhea and its complications.

| Toxicicity | Grade 1 | Grade 2 | Grade 3 | Grade 4 |
| --- | --- | --- | --- | --- |

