7.2 During treatment

The following investigations are required during treatment:

• Medical assessment (including medical history, concomitant medications, analgesic use, adverse event assessment, physical examination, ECOG PS determination, vital signs, and body weight) on days 1 and 8 of cycle 1 and the first day of subsequent cycles.

• Biochemical, hematological analysis on days 1 and 8 of the first cycle and on the first day of subsequent cycles. If the patient has haematological, renal or hepatic toxicity ≥ grade 3, then laboratory tests should be repeated weekly until reduction to ≤ grade 1.

• Chest CT, total abdomen CT and chest X-ray will be performed during patient screening. If the patient has contraindications to the use of tomographic contrast, non-contrast-enhanced chest tomography and total abdomen magnetic resonance imaging will be performed. For response evaluation, tomography of the tumor sites will be performed every 6 weeks until the 18th week of the study, and then every 12 weeks. The same method and technique should be used to characterize each lesion identified and reported on baseline examination and during the study treatment period. Imaging-based evaluation, in addition to clinical examinations , are the techniques required when both can be used to evaluate the antitumor effect of treatment.

• Quality of life assessment with the EORTC QLQ-C30 and CR29 questionnaires translated into Portuguese will be performed on screening, on the first day of cycles 3, 6, 9, every four cycles onwards.

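### Section 6.1 prescribes irinotecan 350 mg/m² on day 1, while the synopsis and the reduction rules are built on 125 mg/m² on days 1 and 8

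*Protocol*

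**What the plan says.** The synopsis gives the irinotecan regimen twice, under Study Design and under Dose, treatment cycle. Both entries agree; the first reads "irinotecan at a dose of 125 mg per square meter body surface area D1 and D8 every 21 days". Under Preparation and administration, the synopsis sets a 90-minute infusion and states: "The irinotecan infusion will be preceded by the infusion of dexamethasone 20mg and ondansetrone 16mg".

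Section 6.1 (Administration of medicines) states "Patients will receive irinotecan 350 mg" per m² intravenously, "in continuous infusion lasting 3 hours on D1 every 3 weeks", and describes this as the routine practice of the service. Its premedication list begins "Dexamethasone 8 mg intravenously 15 minutes before infusion" and continues with ondansetron 8 mg and subcutaneous atropine 0.25 mg.

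Section 6.2 (Dose Adjustments, Irinotecan) begins "The dose levels of irinotecan are 125 mg" per m² and continues with 100 and 75 mg/m². The toxicity table that follows subtracts 25 mg/m² at grades 2 and 3 and 50 mg/m² at grade 4, with a floor of 75 mg/m².

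Section 7.2 schedules medical assessment "on days 1 and 8 of cycle 1 and the first day of subsequent cycles", with laboratory tests on the same days. Table 3 (section 7.4) and the synopsis visit schedule follow the same pattern.

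**The concern.** The administration section of a cytotoxic protocol should agree with the synopsis and with the dose-reduction rules. Here it does not, and nothing in the protocol says which text governs. Section 6.1 does not read like a slip in one digit. It is a complete prescription with its own diluent volume, infusion time, premedication and citation, so a pharmacist could follow it without suspecting an error.

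Three things are at stake:

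- **Patient safety.** Section 6.2 names diarrhoea as the commonest form of irinotecan intolerance. Section 1.2 cites a study in which more than half of metformin recipients had diarrhoea, against just over 11% on placebo. The irinotecan dose therefore bears directly on an overlapping toxicity.
- **Dose reduction.** A patient started at 350 mg/m² falls outside the named dose levels.
- **Interpretation.** Safety is a primary objective alongside week-12 disease control (section 3.1), and there is no control arm. The observed rates mean something only for a defined regimen.

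**Working it through.** No sample size or power figure is involved. The check sets the texts side by side and compares planned doses.

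**1. The two regimens**

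| Item | Synopsis | Section 6.1 |
| --- | --- | --- |
| Dose per infusion | 125 mg/m² | 350 mg/m² |
| Days in a 21-day cycle | 1 and 8 | 1 only |
| Infusion time | 90 minutes | 3 hours |
| Dexamethasone | 20 mg | 8 mg |
| Ondansetron | 16 mg | 8 mg |
| Atropine | not mentioned | 0.25 mg |

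Dose, days, infusion time and premedication all differ together. That rules out one regimen written in two ways, and a fault in reading a single number from the PDF.

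**2. Planned dose** (dose per infusion × infusions per cycle)

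- Synopsis: 2 × 125 = 250 mg/m² per 21 days, or 250 / 3 = 83.3 mg/m² per week.
- Section 6.1: 1 × 350 = 350 mg/m² per 21 days, or 350 / 3 = 116.7 mg/m² per week.
- Ratio per cycle: 350 / 250 = 1.40. Ratio per infusion: 350 / 125 = 2.8.
- Over the four cycles before the week-12 assessment: 4 × 250 = 1,000 mg/m² against 4 × 350 = 1,400 mg/m².

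**3. Reduction rules applied to each starting dose**

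| Start | 25 mg/m² step (grades 2 and 3) | 50 mg/m² step (grade 4) |
| --- | --- | --- |
| 125 mg/m² | to 100, a cut of 25/125 = 20% | to 75, a cut of 50/125 = 40% |
| 350 mg/m² | to 325, a cut of 25/350 = 7% | to 300, a cut of 50/350 = 14% |

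From 125 mg/m² the steps land exactly on the named levels. From 350 mg/m², a patient with grade 4 toxicity could be re-treated at 300 mg/m². The other reading, a drop to the highest named level, is a cut of (350 − 125)/350 = 64%. The protocol does not say which reading applies.

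**4. Visit schedule against each regimen**

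Day-1 dosing is covered in every cycle. Under days 1 and 8, the only routine day-8 assessment is in cycle 1, and section 6.2 ties that visit to the metformin escalation. The blood-count thresholds under Table 2 are conditions for starting a new cycle, not for a day-8 infusion. From cycle 2 onwards, no day-8 infusion has a routine blood count or toxicity assessment. Before week 12 that is 3 of the 8 planned infusions (day 8 of cycles 2, 3 and 4).

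The dose rules therefore fit the synopsis regimen, while the visit schedule fits day-1 dosing. Correcting section 6.1 alone would leave the second mismatch in place.

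**The case against.** The strongest reply is that the intended regimen can be inferred. Both synopsis entries and all of section 6.2 point to 125 mg/m², and section 6.1 stands alone on dose, so it is probably leftover text. That is a fair reading and it helps in choosing the fix. It does not remove the conflict, because the outlier is the section that tells staff what to give.

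Several narrower points deserve weight:

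- **No mixed dosing is documented.** The protocol does not show that any patient received 350 mg/m². If the trial ran at one hospital (section 10.1 calls it single-centre, the synopsis multicentric), mixing between patients is less likely, though uniform use of the wrong regimen remains possible. Mixed dosing would make the results hard to attribute to one regimen, not worthless.
- **Some interim tests exist.** Section 7.2 requires weekly laboratory tests after haematological, renal or hepatic toxicity of grade 3 or higher. These are triggered by earlier toxicity and are not a routine check before a day-8 infusion.
- **The reduction table can be applied to 350 mg/m².** Because it is written as decrements, it could be used, but step 3 of the working shows that it fits badly.
- **Atropine may simply have been left out of the synopsis for brevity.** This is possible and little rests on it. The dexamethasone and ondansetron doses do conflict.

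**Conclusion.** The concern holds. The current text prescribes two irinotecan regimens that differ by 40% in planned dose per cycle and 2.8-fold per infusion, with different days, infusion times and premedication. The dose-reduction rules suit only the 125 mg/m² regimen, and the visit schedule suits only day-1 dosing. The dose comparison is plain arithmetic on stated doses and needs no outside figure.

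That patients could be treated under either text is a risk inferred from the wording, not a documented event. The sample size and decision rule are unaffected. For a cytotoxic drug in a trial with safety as a primary objective, this must be corrected.

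**What to change.** The sponsor's clinicians should choose one regimen; 125 mg/m² on days 1 and 8 of a 21-day cycle has the most support in the protocol. Then:

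1. State the same dose, days, infusion time and premedication in the synopsis and section 6.1.
2. Make the dose levels and reduction steps in section 6.2 fit that starting dose. If 350 mg/m² on day 1 is chosen instead, a new set of levels is needed.
3. If day-8 dosing stands, add a day-8 clinical assessment and blood count in every cycle to the synopsis visit schedule, section 7.2 and Table 3, and state the criteria for giving the day-8 infusion.
4. If any patient was treated under the other text, record the regimen given and report disease control and toxicity by regimen.

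The first three steps cost a protocol correction, a note to the treating team and the added day-8 visits, with no statistical cost. The fourth, if needed, would divide a sample of 41 and reduce the precision of each estimate.
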